#### 2.10.2.
*Analysis for safety*.

Any emerged AEs in this study would be listed with detailed descriptions. The frequency of relevant and irrelevant AEs to the interventions would be recorded. The Fisher’s exact test would be used to analyze whether the incidence of reported AEs is different between the 2 groups. In addition, descriptive analysis would be conducted for the severity and type of AEs to determine the difference between the 2 groups.

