**Discussion::**

The findings of this study on the efficacy and safety of the BMA would be helpful for patients with dry eye in clinical practice. Further, these results would provide for the foundation of a large-scale BMA study.

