## 1. Introduction

Dry eye syndrome is a lacrimal disease caused by insufficient secretion or excessive evaporation of tears, which leads to ocular surface damage, and accompanies irritating symptoms, including discomfort, foreign body sensation, or dryness of the patient’s eye.^[1]^ According to a report from the National Health Insurance Service of Korea in 2018, the prevalence of dry eye has steadily increased by 2.1% annually since the recent 5 years.^[2]^ Nowadays, dry eye can be aggravated by various environmental factors, which include excessive use of visual display terminals, increase in indoor stay, fine dust, or growing use of contact lenses.^[3–5]^ Although artificial tears, corticosteroid eye drops, cyclosporine, therapeutic contact lenses, protective glasses, and punctal occlusion have been suggested as treatments, they have several side effects and are not considered fundamental treatment options.^[6–9]^

In Korean medicine, acupuncture or herbal medication, which clear heat, nourish the yin and body fluid, or supplement the blood and qi, have been traditionally used for dry eye.^[10]^ Clinically, acupuncture has been considered the main Korean medicine treatment for dry eye. Hence, studies^[11–14]^ on the efficacy of acupuncture for dry eye have been steadily reported; however, these prior studies are mainly limited to case reports. Thus, a randomized controlled trial (RCT) is necessary to establish the evidence of acupuncture for dry eye.

Intradermal acupuncture (IDA) is a type of acupuncture commonly used for dry eye in clinical practice; however, related clinical studies are rare. Thus, we conducted preliminary studies on the efficacy and safety of IDA for dry eye. First, we searched RCTs on IDA for dry eye from domestic and foreign databases, and analyzed 4 eligible RCTs.^[15]^ Thereafter, we conducted a preliminary RCT (not published yet) comparing IDA with body acupuncture for dry eye. This study has suggested significant improvement of the ocular surface disease index (OSDI) in both interventions, no difference upon intergroup comparison, and safety of IDA.

This study assesses the efficacy and safety of a biodegradable microneedle acupuncture (BMA) for patients with dry eye compared to conventional IDA. Based on the results, this study aims to demonstrate the superiority of BMA for dry eye compared to conventional IDA.

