### 2.2. Sample size and recruitment

The exact calculation of the number of participants for statistical analysis for this pilot study is challenging because owing to the few reports on BMA. The number of participants for a pilot study should be at least twelve people per group as suggested by a previous study.^[16]^ Considering a dropout rate of 20% owing to a total of 12 treatments for 4 weeks, this study requires fifteen participants per group. Thus, the total required participant number for this study is thirty.

Participants would be recruited via advertisements in a single hospital. If a patient desires to participate, investigators would detail the study. Then, the participant who voluntarily submits the written consent would be screened using the inclusion and exclusion criteria. If considered suitable, the participant would receive a unique participant number.

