### 2.4.
*Randomization and allocation concealment*

Block randomization will be used to divide the participants into 2 groups. The randomization will be conducted by a statistical software (SAS; SAS Institute Inc., Cary, NC). Setting the block size as 4, total 30 people would be randomly allocated into 2 groups with the same possibility. Thus, 15 participants would be assigned to each group.

Allocation would be decided after screening. Investigators will open an opaque and sealed envelope, which contains the allocation result, in front of the suitable participant. The opened envelope will be stored separately.

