#### 2.10.1.
*Analysis for the primary and secondary outcomes*.

The same analysis method will be used for the primary and secondary outcomes. The measurements from each group would be presented as descriptive statistics, including mean, median, standard deviation, minimum, and maximum. In the intragroup comparisons, the differences in the outcomes following the interventions would be analyzed using the Student’s paired *t* test or the Wilcoxon signed-rank test, and 95% confidence intervals would be presented. The differences between the 2 groups on each visit would be statistically assessed using the 2-sample *t* test or the Mann–Whitney test, depending on whether the normality is satisfied. For missing values, a last observation carried forward method would be used to handle.

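### Comparative safety rests on one Fisher's exact test at 15 per arm, which is valid but uninformative; risk differences with intervals should carry the comparison

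*Protocol article*

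**What the plan says.** The Introduction puts safety beside efficacy as a comparative aim: "This study assesses the efficacy and safety of a biodegradable microneedle acupuncture (BMA) for patients with dry eye compared to conventional IDA". The Discussion paragraph of the Abstract gives the result a practical use: "The findings of this study on the efficacy and safety of the BMA would be helpful for patients with dry eye in clinical practice".

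Section 2.10.2 sets the safety analysis. Each AE is listed with a description, and frequencies are recorded for events related and unrelated to the interventions. Then comes the one inferential step: "The Fisher’s exact test would be used to analyze whether the incidence of reported AEs is different between the 2 groups". Finally, "descriptive analysis would be conducted for the severity and type of AEs to determine the difference between the 2 groups".

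No between-arm estimate or interval is named for AEs. Section 2.10.1 does name intervals, for within-group changes in the efficacy outcomes, which "would be analyzed using the Student’s paired *t* test or the Wilcoxon signed-rank test, and 95% confidence intervals would be presented".

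On size, section 2.4 says: "Thus, 15 participants would be assigned to each group". Section 2.2 reaches that number from 12 per group and 20% dropout. Section 2.9.3 lists the types of AE expected in each arm, with some expected for BMA in addition to those of IDA, but gives no rates.

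**The concern.** With 15 participants per arm, a test of whether AE incidence differs will often be non-significant even when one device causes clearly more events. If that test is the only formal comparison, the reader learns neither how large an excess the data suggest nor how large an excess they leave open.

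This matters because safety is half of the stated aim, BMA is described as a new device, and section 2.9.3 itself expects some additional local skin events with it. The planned larger trial also needs AE rates and their uncertainty more than it needs a p value.

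**Working it through.** **Inputs.** From the protocol: 15 per arm (section 2.4); 12 per arm and 20% dropout (section 2.2); Fisher's exact test on AE incidence (section 2.10.2). Assumed, because the protocol does not give them: a two-sided test, alpha 0.05, and the AE rates, read as the proportion of participants with at least one AE. A range of rates is therefore shown.

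**The plan's own figure.** 12 / (1 − 0.20) = 15 per arm, 30 in total. This reproduces. It is not based on safety.

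**Method.** For n per arm and true rates p₀ (IDA) and p₁ (BMA), power is the sum, over all pairs (a, b) with Fisher p ≤ 0.05, of Bin(a; n, p₁) × Bin(b; n, p₀). The miss rate is 1 − power.

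**A 20-point excess:**

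| IDA → BMA | Miss rate, n = 15 | Miss rate, n = 12 |
|---|---|---|
| 10% → 30% | 85.1% | 90.5% |
| 20% → 40% | 88.8% | 90.8% |
| 30% → 50% | 90.3% | 90.6% |
| 40% → 60% | 90.5% | 90.3% |
| 50% → 70% | 90.3% | 90.6% |
| 60% → 80% | 88.8% | 90.8% |

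**Ratios, n = 15.** Here the control rate dominates.

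- Doubling: 5% → 10%, missed 99%; 20% → 40%, 89%; 30% → 60%, 77%; 40% → 80%, 55%.
- Tripling: 5% → 15%, missed 97%; 10% → 30%, 85%; 20% → 60%, 55%.

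No single miss rate describes a doubling or a tripling.

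**Large excess, n = 15.** 10% → 60% is missed 26% of the time, so power is 74%. With equal rates of 20% the test rejects 1.7% of the time, well under the nominal 5%.

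**Smallest splits that reach p ≤ 0.05, n = 15.** Against 0, 1 or 2 IDA participants with an AE, BMA needs 5, 7 or 9. For 5 against 0, p = 2 × C(15,5) / C(30,5) = 2 × 3,003 / 142,506 = 0.042.

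**What an interval adds, n = 15.** The Newcombe limits combine the Wilson limits (l, u) of each arm, with d = p̂₁ − p̂₀:

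- lower = d − √[(p̂₁ − l₁)² + (u₀ − p̂₀)²]
- upper = d + √[(u₁ − p̂₁)² + (p̂₀ − l₀)²]

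For 8/15 against 2/15, d = 0.533 − 0.133 = 0.400, with Wilson limits 0.301 to 0.752 and 0.037 to 0.379.

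- lower = 0.400 − √(0.232² + 0.245²) = 0.06
- upper = 0.400 + √(0.219² + 0.096²) = 0.64

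| BMA vs IDA | Fisher p | Risk difference, points (95% CI) |
|---|---|---|
| 8/15 vs 2/15 | 0.0502 | +40 (+6 to +64) |
| 6/15 vs 2/15 | 0.21 | +27 (−5 to +53) |
| 6/15 vs 3/15 | 0.43 | +20 (−12 to +47) |
| 3/15 vs 0/15 | 0.22 | +20 (−4 to +45) |
| 0/15 vs 0/15 | 1.0 | 0 (−20 to +20) |

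Every row is non-significant by Fisher's test, and every interval leaves open an excess of at least 20 points. With no events in 15, the exact two-sided 95% upper limit for that arm is 1 − 0.025^(1/15) = 21.8%.

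**The case against.** The strongest reply is that nothing in section 2.10.2 is wrong. Fisher's test is a proper choice for small counts. The section also plans listings, related and unrelated frequencies and a descriptive comparison. Detail on intervals may sit in a full protocol or analysis plan that is not shown. Low power is inherent in a 30-patient pilot, and the article's Discussion (section 3) concedes the small sample and plans a confirmatory trial. Intervals would be inconclusive too, and could be derived afterwards from the reported counts.

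Most of this stands, and it keeps the point modest. The point does not rest on the mere absence of an interval. It concerns the method that the article does name for the comparison, which suits this sample poorly. A wide interval shows that the result is inconclusive; a p value alone does not.

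Three stronger readings are tempting, and the document does not support them.

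- A reader might infer that the trial will declare equal safety when p exceeds 0.05. The protocol states no alpha and no such rule. The Introduction's summary of the preliminary trial, "no difference upon intergroup comparison, and safety of IDA", does not supply one: the absence of a difference follows on from the OSDI result, and safety is listed as a separate item.
- A reader might say that the test misses any doubling or tripling 85% to 90% of the time. That fits 20% → 40% and 10% → 30%, not ratios in general. With ten sites treated at each of 12 sessions, local reactions could be common, and miss rates for ratios would then be lower.
- A reader might call non-significance near certain however harmful BMA is. Power of 74% at 10% → 60% contradicts that.

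The figures at 12 per arm are likewise only a sensitivity case. AEs are recorded at every visit, and the protocol does not say that the exclusions in section 2.11.2 apply to the safety analysis.

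**Conclusion.** The point holds as a worthwhile, low-cost improvement, not as an error in the test. Given a two-sided 0.05 level and control rates of 10% to 60%, all assumed, Fisher's test at 15 per arm misses a 20-point excess between 85% and 91% of the time. Common local reactions within that range do not rescue it against an absolute excess of that size, although miss rates for a given ratio vary widely. A non-significant result would therefore be compatible with both equal and materially unequal harm, and could not support a statement that BMA is as safe as IDA. The protocol does not make that statement. Nor does it name an analysis that would show how far the data fall short of it.

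**What to change.** In section 2.10.2, make estimation the comparative safety analysis. For participants with at least one AE, and separately for those with at least one intervention-related AE:

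- report incidence per arm with an exact (Clopper-Pearson) 95% confidence interval, which also gives an upper limit where an arm has no events;
- report the BMA minus IDA risk difference with a 95% confidence interval, for example Newcombe's.

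Keep Fisher's p as descriptive, keep the planned listings and summaries, and add a sentence such as: *A non-significant test will not be taken as evidence that the two devices are equally safe; the safety conclusion will be worded from the confidence interval for the risk difference.*

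The cost is a few sentences and one extra table, from data already collected at each visit. No further participants or procedures are needed. The downside is that the intervals will be wide and the safety statement correspondingly more cautious.

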### 2.11.
*Suspension and dropout*

#### 2.11.1.
*Criteria for discontinuing*.

Violating inclusion criteria or satisfying exclusion criteria.Emergence of serious AEs, or challenging in trial continuation due to AEs.A participant or his/her legal representative demands for discontinuing the trial owing to unsatisfactory therapeutic effect.Compliance with the trial is below 80%.Violations of the study protocol by investigators or participants.Withdrawal of participant’s agreement to the study.Loss to follow-up.During the treatment visits or the follow-up visit, the medications which can influence on the outcomes assessment were used without the investigators’ permission.Others considered inappropriate to proceed the trial by the investigators.

#### 2.11.2.
*Criteria for exclusion from analysis*.

If a severe protocol violation occurs, the participant would be excluded from the final analysis, and the data would be analyzed using an intention-to-treat analysis. The followings are severe violations of the protocol:

Violations of the eligibility criteria.Used prohibited concomitant medications during the trial.The assessment for primary outcome was omitted at the beginning and/or end of the trial.The number of treatment did not exceed 80% of total scheduled treatments.

For minor violations, investigators would accurately record the degree of violation and its reason. Thereafter, an investigator, a statistician, and a monitor would comprehensively consider the influence on the trial when writing the outcome report. The data would be analyzed using a per-protocol analysis.

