### 2.7.
*Prohibited and permitted concomitant treatment*

During the trial, all kinds of concomitant treatments, including Korean medical therapy, would not permitted to both groups. The concomitant use of medications including anti-inflammatory eye drops, corticosteroids, or immunosuppressants would be prohibited. Participants who used such unauthorized medications would be dropped out from the study, and excluded from the final analysis.

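### Section 2.11.2 removes randomised participants from the final analysis yet calls that analysis intention-to-treat, and the removal conflicts with the stated LOCF rule

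*Protocol article*

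**What the plan says.** Section 2.11.2 of the protocol article governs exclusion from analysis. For a severe violation it says that "the participant would be excluded from the final analysis, and the data would be analyzed using an intention-to-treat analysis". It lists four severe violations:

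- "Violations of the eligibility criteria"
- "Used prohibited concomitant medications during the trial"
- "The assessment for primary outcome was omitted at the beginning and/or end of the trial"
- "The number of treatment did not exceed 80% of total scheduled treatments"

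It then turns to minor violations, which an investigator, a statistician and a monitor weigh together, and closes with "The data would be analyzed using a per-protocol analysis".

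Section 2.7 states the medication exclusion a second time: "Participants who used such unauthorized medications would be dropped out from the study, and excluded from the final analysis".

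Three other sections bear on the point. Section 2.10.1 handles missing values by LOCF. Section 2.9.1 schedules the OSDI at visits 1, 7 and 13. Section 2.11.1 lists, among the reasons for discontinuing, "A participant or his/her legal representative demands for discontinuing the trial owing to unsatisfactory therapeutic effect". No section names a primary analysis set.

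**The concern.** Intention-to-treat means that everyone randomised is analysed in the arm to which they were assigned. Section 2.11.2 uses that name for an analysis from which randomised people have been taken out. Three of the grounds arise after randomisation: medication use, too few treatments and a missing final OSDI. Removing people for such events gives something close to a per-protocol set.

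Two things are at stake. First, the report could present as intention-to-treat a result that is not one, and two analysts following section 2.11.2 could build different datasets. Second, the exclusions could be related to outcome and differ by arm. Participants and therapists know the treatment (section 2.5), the primary outcome is a participant questionnaire, and lack of effect is a recognised reason for leaving. Someone who leaves before the tenth treatment is removed on attendance alone. Poorly controlled symptoms are also a plausible reason for taking a prohibited medication. If that happened more in one arm, the comparison would lose the protection of randomisation.

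**Working it through.** **Sample size (section 2.2).** The stated inputs are 12 per group and 20% dropout: 12 / (1 − 0.20) = 15 per group, 30 in total. The stated figure reproduces. The plan thus allows for losing 15 − 12 = 3 per group. Analysing everyone as randomised keeps 15 v 15. If the whole allowance were excluded, 12 v 12 (24 of 30) would remain.

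**Attendance cut-off.** 80% of 12 = 9.6. Nine treatments (9/12 = 75%) do not exceed it and ten (10/12 = 83%) do, so 9 or fewer means exclusion.

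**The sections side by side, for a participant with no visit 13 OSDI.**

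- Sections 2.9.1 and 2.10.1: an OSDI from visit 1, and possibly visit 7, exists and is carried forward, so the participant is analysed.
- Section 2.11.2: the final OSDI is missing, so the participant is removed from the final analysis.
- Section 2.11.2, same sentence: the analysis is intention-to-treat, so the participant should be included.

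These cannot all be followed. For a medication user, section 2.7 and the list in 2.11.2 both say exclude, and only the intention-to-treat label says include.

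**How large could a bias be?** The protocol gives no alpha, SD, effect size or exclusion pattern, so this is an illustration on stated assumptions: no true difference, normal outcome with SD 1 (higher is better), 15 per arm, 3 excluded per arm, and a two-sample t test at two-sided 0.05, counting only results that favour BMA. In the BMA arm, the 3 participants lowest on an exclusion score leave; the score has correlation r with the outcome. In the control arm, 3 leave at random.

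At r = 1 the three worst responders leave, and simulation puts the mean of the remaining 12 about 0.33 SD too high. For smaller r the shift is r × 0.33 SD, for example 0.3 × 0.33 = 0.10 and 0.7 × 0.33 = 0.23.

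| r | Shift (SD) | False BMA superiority |
|---|---|---|
| 0 | 0.00 | about 2.5% |
| 0.3 | 0.10 | about 4% |
| 0.5 | 0.17 | about 6% |
| 0.7 | 0.23 | about 9% |
| 1.0 | 0.33 | about 15% |

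If the same selection operates in both arms, the mean shift is about 0 and the figure is 2.5% to 5% across the same values of r. With all 30 analysed it is about 2.5%.

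**The case against.** The strongest defence is that section 2.11.2 is a garbled account of two ordinary sets, with violators kept under intention-to-treat and dropped from per-protocol. The LOCF rule supports this, because it would have almost nothing to do for the visit 13 OSDI if everyone lacking that value were deleted. But the text does not say so, and section 2.7 excludes medication users with no intention-to-treat exception. The defence shows that the intention may have been sound. It does not rescue the rule as written.

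Several stronger readings are tempting but unsupported:

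- **That the main result is certain to be a completer comparison.** No set is named main or primary. The phrase about the final analysis points that way, but the documents contradict each other.
- **That the two sets are swapped.** A swap would make per-protocol the all-randomised set, and nothing says that. The per-protocol sentence merely follows the text on minor violations.
- **That unblinded investigators decide who is excluded.** The four severe criteria are factual rules. Joint judgement applies to minor violations, and open discretion appears in section 2.11.1, which concerns discontinuation.
- **That anyone leaving for lack of effect has no final OSDI.** Section 2.11.1 does not say that leavers skip visit 13, though the attendance rule could still remove them.
- **That the false-positive rate is 15%.** That needs perfect selection in one arm and random loss in the other. Section 2.2 attributes the 20% dropout to the number of treatments, and both arms are active with the same acupoints, retention time and schedule.

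It is also a pilot of 30 with a confirmatory trial planned. That lowers the stakes, but the article states a superiority aim and the results are meant to inform the next trial.

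**Conclusion.** The point holds as a contradiction over who is analysed. Section 2.11.2 excludes randomised participants and calls the result intention-to-treat, section 2.7 reinforces the exclusion, and section 2.10.1 assumes that participants with a missing value stay in. If the exclusions are applied as written, the set is per-protocol-like and the label is false, whatever the data turn out to be.

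That the exclusions would bias the result is a possibility and not an established fact. It requires exclusion to be related to outcome and to differ by arm. The design leaves room for that, but the documents give no figure for it. On the assumptions above, the shift lies between 0 and 0.33 SD and the chance of false BMA superiority between about 2.5% and 15%, with the top of the range an extreme. The need to correct the rule does not depend on where in that range the trial would fall.

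**What to change.** 1. Define intention-to-treat as all randomised participants in their assigned arm, and name it the primary set for OSDI.
2. Use the four criteria in section 2.11.2 only to define a per-protocol set, reported as a sensitivity analysis. Decide membership without knowledge of the arm and before the data are locked.
3. Remove the exclusion from the final analysis in section 2.7. This concerns only who is analysed and leaves the discontinuation rules untouched.
4. Seek visit 13 outcomes from participants who stop, where still obtainable.
5. State one rule for a missing visit 13 OSDI, the same in sections 2.10.1 and 2.11.2: the LOCF already named, or a likelihood-based or multiple-imputation analysis using visits 1 and 7. Add a sensitivity analysis. Without this step an all-randomised set cannot be analysed consistently.

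The cost is mainly wording before database lock, plus some effort to obtain final outcomes. Enrolment began in July 2022 (section 2.13), so some of those outcomes may already be out of reach. The estimate will include non-adherence and may be slightly diluted.

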## 2. Method

### 2.1. Study design

This study is designed as an investigator-initiated, parallel, superiority RCT. Patients with dry eye who voluntarily agree to this study would be screened using the necessary examinations and eligibility criteria. The suitable participant would be randomly allocated to the experimental group or the control group on visit 1. The participants allocated to the experimental group would be treated with the BMA. In contrast, the participants allocated to the control group would be treated with IDA. For 4 weeks, both the groups would be treated 3 times a week (total 12 times) by each intervention. Within 4 weeks from visit 1, the investigators would conduct the final assessment after treatment termination, and the trial would be completed.

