#### 2.9.3.
*Safety assessment*.

AE includes any unintended results that occurred even though the medical device was appropriately used according to the instructions. The expected AEs of the IDA are local pain from the treated area, local bleeding from the treated area, allergic reactions of the skin, infections, localized infection symptoms (redness, swelling, and/or local pain), nausea, vomiting, headache, and/or dizziness.^[22,23]^ For the BMA, redness on the treated area, skin irritation, and/or skin erosion are also expected in addition to the expected AEs of the IDA. Investigators would check and record the emergence of AEs on the CRF at each visit.

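### The section 2.11.2 exclusions are not limited to efficacy, so participants who stop early because of harm can drop out of the between-group adverse event comparison

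*Protocol article*

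**What the plan says.** Section 2.1 sets the exposure: "both the groups would be treated 3 times a week (total 12 times) by each intervention".

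Section 2.11.1 gives among its grounds for discontinuing a participant: "Emergence of serious AEs, or challenging in trial continuation due to AEs".

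Section 2.11.2, headed as criteria for exclusion from analysis, states the consequence of a severe violation: "If a severe protocol violation occurs, the participant would be excluded from the final analysis". The same sentence goes on to say that "the data would be analyzed using an intention-to-treat analysis". Two of the four severe violations matter here: "The number of treatment did not exceed 80% of total scheduled treatments" and "The assessment for primary outcome was omitted at the beginning and/or end of the trial".

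Section 2.10.2 lists every adverse event that emerges and compares the incidence of reported events between the groups with Fisher's exact test. It also says: "The frequency of relevant and irrelevant AEs to the interventions would be recorded". It does not say which participants enter the test. Section 2.9.3 has adverse events recorded on the case report form at each visit.

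**The concern.** Taken together, sections 2.11.1 and 2.11.2 form a chain. An adverse event can end a participant's treatment. Ending it early enough makes that participant a severe violator, and severe violators are left out of the final analysis. Nothing in section 2.11.2 restricts this to efficacy or excepts those who stopped because of harm.

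Safety is half of the stated aim, and section 2.9.3 expects additional skin reactions with the microneedle device. If those who stop because of an event are removed from both the numerator and the denominator of the incidence, the arm that causes more stopping looks safer than it is. The missing-OSDI criterion is a second route to the same result, since a participant who withdraws because of an event may have no final assessment.

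Intention-to-treat does not settle the matter. It is claimed in the very sentence that excludes participants, so the reader cannot tell which half governs.

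**Working it through.** **Inputs from the protocol article**
- Scheduled sessions: 12 (section 2.1).
- Exposure criterion: sessions must exceed 80% of schedule (section 2.11.2).
- Sample size: at least 12 per group, 20% dropout, 15 per group (section 2.2).
- Adverse event rates, alpha and sidedness: not given. The event counts and the two-sided test below are assumptions.

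**The plan's own figure.** 12 / (1 − 0.20) = 15 per group, 30 in total. This reproduces. The allowance is 0.20 × 15 = 3 participants per group.

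**Who is caught by the exposure rule.** 0.80 × 12 = 9.6 sessions.
- 9 sessions: 9/12 = 75.0%, excluded.
- 10 sessions: 10/12 = 83.3%, kept on this criterion.
- 11 sessions: 11/12 = 91.7%, kept on this criterion.

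So a stop for an adverse event after 9 or fewer sessions is a severe violation. After 10 or 11 it is not, unless another criterion applies, such as a missing final OSDI.

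**Effect on the Fisher comparison.** All 15 per arm are taken as treated, because randomisation and first treatment are both at visit 1. Every excluded participant is assumed to be in one arm and to have had an event.

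| Stopped and excluded | All treated | After exclusion |
|---|---|---|
| 3 | 5/15 v 0/15, p=0.042 | 2/12 v 0/15, p=0.188 |
| 3 | 3/15 v 0/15, p=0.224 | 0/12 v 0/15, p=1.000 |
| 3 | 7/15 v 1/15, p=0.035 | 4/12 v 1/15, p=0.139 |
| 2 | 6/15 v 0/15, p=0.017 | 4/13 v 0/15, p=0.035 |
| 1 | 5/15 v 0/15, p=0.042 | 4/14 v 0/15, p=0.042 |

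The first row by hand:
- Before exclusion there are 5 events among 30, all in one arm. Both tails are equally extreme: 2 × C(15,5)/C(30,5) = 2 × 3,003/142,506 = 0.042.
- After exclusion there are 2 events among 27, both in the arm of 12: C(12,2)/C(27,2) = 66/351 = 0.188. The opposite tail, C(15,2)/C(27,2) = 105/351 = 0.299, is more probable than the observed table, so it is not added.

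The observed difference in that row falls from 33.3 points (5/15) to 16.7 points (2/12). In the last row it falls from 33.3 to 28.6 points (4/14).

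**The case against.** The strongest reply is that no sentence applies section 2.11.2 to safety. Its criteria read like those of an efficacy population: eligibility, prohibited medication, primary outcome and exposure. Safety has its own section, which states no exclusion, and a safety population is commonly defined in a full protocol or analysis plan that is not shown here. This stands in part. The lack of a named safety set is not an error in the article, and the harm arises only if the final analysis is read to include safety. But the point does not rest on silence. Section 2.11.2 states a general exclusion under a general heading, and its own wording does not rule that reading out.

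A reader might infer three stronger things, none of which the document supports.
- **That everyone who stops for an adverse event is excluded.** Stops after 10 or 11 sessions pass the exposure rule.
- **That the events themselves are lost.** They are recorded at each visit and all are listed, and section 2.8.5 allows extra visits for persisting events.
- **That events count only when the device was used correctly.** Section 2.9.3 says "AE includes any unintended results that occurred even though the medical device was appropriately used according to the instructions". The verb is inclusive, and section 2.10.2 counts events both related and unrelated to the interventions.

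The illustration is also open to challenge. Three excluded participants use the whole dropout allowance of one arm, while section 2.2 ties dropout to the number of treatments, not to harm. With one such participant the p-value does not change. That is accepted: the figures show what could happen, not what is expected.

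**Conclusion.** The concern holds in a limited form. As written, section 2.11.2 can remove participants who stopped because of harm, after 9 or fewer of 12 sessions or without a final OSDI, from the between-group incidence test. It also contradicts its own claim of intention-to-treat. What is at risk is the comparison, not the record of events.

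The size depends on counts that the document does not give. It ranges from slight, with one excluded participant, to the loss of an apparent signal with three in one arm (p=0.042 to p=0.188, or 3/15 v 0/15 becoming 0/12 v 0/15). The conclusion rests on reading the final analysis to cover safety, which the text allows but does not state. It does not extend to the definition of an adverse event.

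**What to change.** Three changes of wording:
1. In section 2.11.2, state that the listed exclusions define only the per-protocol efficacy set.
2. In the same sentence, reconcile the exclusion with intention-to-treat by saying which analysis uses all randomised participants and which uses the reduced set.
3. In section 2.10.2, state that adverse event incidence is compared in all participants who received at least one application, by device received, regardless of section 2.11.2.

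Optionally, align the definition in section 2.9.3 with section 2.10.2, which already counts related and unrelated events.

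No new data are needed, because adverse events are already recorded at every visit. The trial is ongoing, so the changes should be dated and in place before the data are analysed.
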